## Abstract

**Background:**

Many patients experience pain in the intensive care unit (ICU) despite receiving pain medication. Research has shown that music can help reduce pain. Music interventions studied so far have not used music streaming to generate playlists based on patient preferences while incorporating recommended tempo and duration. Previous research has focused on postoperative ICU patients able to self-report, which is underrepresentative of the ICU population that might benefit from a music intervention for pain management. We developed a new patient-oriented music intervention (POMI) that incorporates features based on theoretical, empirical, and experiential data intended to be used in the ICU. Such a music intervention should consider the expertise of ICU patients, family members, and nursing staff, as well as the practicality of the intervention when used in practice.

**Objective:**

The primary objectives of this study are to (1) evaluate the acceptability and feasibility of the POMI to reduce pain in ICU patients and (2) evaluate the feasibility of conducting a crossover pilot randomized controlled trial (RCT) for intervention testing in the ICU. A secondary objective is to examine the preliminary efficacy of the POMI to reduce pain in ICU patients.

**Methods:**

A single-blind 2×2 crossover pilot RCT will be conducted. Patients will undergo 1 sequence of 2 interventions: the POMI which delivers music based on patients’ preferences via headphones or music pillow for 20-30 minutes and the control intervention (headphones or pillow without music). The sequence of the interventions will be inverted with a 4-hour washout period. Timing of the interventions will be before a planned bed turning procedure. Each patient will undergo 1 session of music. Twenty-four patients will be recruited. Patients able to self-report (n=12), family members of patients unable to self-report (n=12), and nursing staff (n=12) involved in the bed turning procedure will be invited to complete a short questionnaire on the POMI acceptability. Data will be collected on the feasibility of the intervention delivery (ie, time spent creating a playlist, any issue related to headphones/pillow or music delivery, environmental noises, and intervention interruptions) and research methods (ie, number of patients screened, recruited, randomized, and included in the analysis). Pain scores will be obtained before and after intervention delivery.

**Results:**

Recruitment and data collection began in March 2022. As of July 5, 2022, in total, 22 patients, 12 family members, and 11 nurses were recruited.

**Conclusions:**

Methodological limitations and strengths are discussed. Study limitations include the lack of blinding for patients able to self-report. Strengths include collecting data from various sources, getting a comprehensive evaluation of the intervention, and using a crossover pilot RCT design, where participants act as their own control, thus reducing confounding factors.

**Trial Registration:**

ClinicalTrials.gov NCT05320224; https://clinicaltrials.gov/ct2/show/NCT05320224

**International Registered Report Identifier (IRRID):**

DERR1-10.2196/40760

## Introduction

### Background and Rationale

Pain is a common symptom in critically ill adults, both in patients able and unable to self-report [1]. Guidelines recommend the use of a multimodal approach to pain management to reduce opioid use and optimize pain relief [1]. Music has been suggested as a nonpharmacologic intervention in acute and chronic care settings, but little is known about its efficacy and feasibility in the intensive care unit (ICU) [2-8]. We conducted a systematic review and meta-analysis of randomized controlled trials (RCTs) to establish the efficacy of music in the adult ICU. Music interventions of 20 to 30 minutes were effective to reduce pain by almost 2 points on a 0-10 numeric rating scale (NRS) in ICU patients able to self-report [9]. However, the effect of music on pain in ICU patients unable to self-report remains unknown. In a previous review, some studies reported that family members of ICU patients expressed their interest in participating in the music selection process and in the pain management of their loved ones [10]. Therefore, music interventions for patients unable to self-report could involve the participation of family members based on their intimate knowledge of the patient and their music preferences.

Current recommendations for music interventions in postoperative patients are to provide music in the range of 60-80 beats per minute (bpm) [11]. However, most ICUs do not have access to music therapists, who have the expertise to provide personalized music within this range. Thus, there is a need to develop an easy-to-use music intervention that produces individualized music playlists with a tempo of 60-80 bpm for ICU patients. Music streaming services allow for the music selection of specific tempo ranges and should be explored as a simple means to provide a more accessible music intervention in the adult ICU.

Studies conducted thus far have mainly focused on postsurgical patients, mechanically ventilated, and able to communicate despite the fact that many patients are likely to be unable to communicate during their ICU stay [9,12,13]. Therefore, RCTs conducted until now on the effect of music to reduce pain in critically ill adults have limited generalizability to the entirety of the ICU population, despite the knowledge that all patients can experience pain and could benefit from this nonpharmacological pain management intervention.

Another limitation in previous RCTs analyzed in the systematic review relates to sample size [9]. In 4 RCTs, no sample size calculation was reported [14-17]. In 3 RCTs, the sample size was calculated based on outcomes other than pain [18-20]. In another 3 studies, the calculated sample size required was not attained for various feasibility issues attributed to “slow” or “difficult” recruitment (due to time limit, refusal rate due to randomization or family visits, and narrow inclusion criteria), or withdrawal of ICU adult patient participants who did not like the music chosen for them [21-23]. In 1 study, it was unclear whether the sample size represented the number of ICU adult patient participants or the number of observations [24]. Inadequate power may explain why 11 of the 18 RCTs found a significant pain reduction while 7 did not. Therefore, there is a need to evaluate the feasibility of research methods by conducting a pilot RCT prior to evaluating the efficacy of any new music intervention in the adult ICU.

### Objectives

This study aims to (1) evaluate the acceptability and feasibility of a new patient-oriented music intervention (POMI) to reduce pain in ICU patients (primary objective); (2) evaluate the feasibility of conducting a crossover pilot RCT for intervention testing in the adult ICU (primary objective); and (3) examine the preliminary efficacy of the POMI (secondary objective).

### Trial Design

A single-blind 2×2 crossover pilot RCT was selected for this study protocol, where patients undergo a sequence of 2 intervention periods: the POMI and the control intervention (CTL: headphones or pillow without music), with an allocation ratio of 1:1.

## Methods

### Design

A single-blind 2×2 crossover pilot RCT is being conducted to evaluate the acceptability, feasibility, and preliminary efficacy of the POMI. Recruitment is planned to occur over a period of 6 months during which we aim to enroll a total of 24 patient participants. As shown in Figure 1, each participating patient is randomly assigned to 1 sequence (sequence 1 or 2) of 2 intervention periods: the POMI and the CTL (headphones or pillow without music). Patients in sequence 1 receive the POMI during the first intervention period, followed by the CTL in the second intervention period; and patients in sequence 2 receive the CTL first, followed by the POMI. Each 20-30–minute intervention period is provided before a bed turning procedure that is planned as part of the participating patient’s usual care by the nursing staff. There is a 4-hour minimum washout period between both intervention periods, with data collected during the day and evening. Data collection begins as soon as possible following recruitment, always in coordination with patient care. Therefore, the first period of data collection may occur in the daytime or in the evening.

**Figure 1 figure1:**
[figure not shown]
Study design for the 2×2 crossover pilot randomized control trial.

**Figure 2 figure2:**
[figure not shown]
Example of web-based tool screenshots for the patient-oriented music intervention.

### Recruitment

Recruitment is conducted by the first author ([name]), who is introduced to the eligible patient and family member by the nurse caring for the eligible patient. If the eligible candidate is interested in hearing about the study, the student researcher meets with them at the ICU bedside to present the study, provides a copy of the informed consent form, and answers any question. The eligible candidate is then given time to think about whether they are interested in the study. ICU nursing staff (ie, nurses and orderlies) involved in the turning procedure during the study are invited individually prior to the scheduled bed turning procedure. Eligible nursing staff are given the informed consent form and can choose to participate at their convenience. Eligible criteria are detailed in Table 1.

**Table 1 table1:** Eligibility criteria.

			Type of participant						
			Patient able to self-report		Patient unable to self-report		Family member		Nursing staff
**Inclusion criteria**									
	Is ≥18 years old	✓		✓		✓		✓	
	Is admitted to ICU^a^	✓		✓					
	Has a loved one admitted to the ICU					✓			
	Works in the ICU							✓	
	Is able to self-report	✓				✓		✓	
	Is able to listen to music as per patient or a family member for patients unable to self-report	✓		✓					
	A family member is present at the bedside			✓					
	Considers self to have knowledge of the patient's music preferences					✓			
	Is qualified to consent to any care required by the state of health for the incapable ICU adult patient					✓			
	Is present during the turning procedure at the time of the POMI^b^ project data collection							✓	
**Exclusion criteria**									
	Cannot be turned	✓		✓					
	Does not speak or understand French or English	✓		✓		✓		✓	
	Is unarousable, as defined by a score of −5 on the Richmond Agitation Sedation Scale (RASS)	✓		✓					
	Is under the effects of neuromuscular blocking agent	✓		✓					

^a^ICU: intensive care unit.

^b^POMI: patient-oriented music intervention.

### Participants

#### Sample Size

A minimal sample size of 10 participants per group is recommended in pilot studies [25,26]. Because studies with repeated measures (such as crossover designs) require more time commitment from participants (ie, multiple measurements over time), an attrition rate of approximately 15% (n=2 per group) can be anticipated, which is consistent with what has been reported in previous studies conducted in the targeted population [27,28]. To account for this, the recruited sample size was estimated to be 12 participants per group.

#### Patients

A sample size of 24 patients is targeted, with 12 being able to self-report and 12 unable to self-report. Patients able to self-report will be asked about their music preferences, levels of pain intensity, distress, and acceptability of the POMI.

#### Family Members

Family members are defined by the patient or, in the case of those unable to self-report, by their surrogates. In such cases, the family may be related or unrelated to the patient. Family members are the individuals who provide support and with whom the patient has a significant relationship [29]. A sample size of 12 family members is targeted: 1 for each patient unable to self-report. Family members will be responsible for providing information on the music preferences of their loved one unable to self-report, as well as answering questions on the POMI acceptability.

#### Nursing Staff

A total of 12 members of nursing staff involved in a participating patient’s bed turning procedure will be recruited to answer questions on the acceptability of the POMI from their perspective.

### Randomization

For the equal allocation of both groups, 24 opaque envelopes were prepared in advance by an independent member of the research team, with the use of a digitally generated list [30]. Once patients or their representatives consent to participate and agree to randomization, patient participants are categorized as either able to self-report or unable to self-report, producing 2 strata. Within each stratum, patients are randomized to either sequence 1 or sequence 2, following a permuted block randomization to ensure balance within each stratum. A block size of 4 was used (3 blocks per stratum) for a sample size of 24 ICU adult patient participants (in each block, 2 patient participants will be assigned to sequence 1 and 2 patient participants will be assigned to sequence 2, and the ordering will be random).

### Patient-Oriented Music Intervention

#### Overview

The brief name given to this intervention is POMI (patient-oriented music intervention). In POMI, music is delivered to adult patients either via headphones (Bose, QuietComfort 35) or by a music pillow (MusiCure, hospital grade). Adult patients admitted to the ICU and able to self-report can choose the mode of delivery based on their personal preference. Adult patients admitted to the ICU and unable to self-report are given the music pillow. For patients able to self-report, individualized music playlists are created based on the patient’s music preferences. For patients unable to self-report, a family member is asked about the patient’s music preferences. Questions about music preferences include music genre, track title, artist name, instrumentalness, acousticness, energy, and valence, as defined by the streaming service Spotify.

#### Playlist Creation

The personalized music playlist is generated prior to the POMI period for each patient participant. To determine the participant’s music preferences, the following questions are asked, based on possible recommendations through the Spotify Application Programming Interface [31]:

Is there any music genre that you would like to listen to?Is there any specific song title that you would like to listen to?Is there any music artist that you would like to listen to?Would you like to hear music that is more instrumental, more vocal, or do you have no preference?Would you like to hear music that is more acoustic, more electric, or do you have no preference?Would you like to hear music that is more calming, more energetic, or do you have no preference?Would you like to hear music that is more cheerful, more melancholic, or do you have no preference?Would you like to hear music that is more popular, less popular, or do you have no preference?Would you like to hear music that is recorded in studio, do you prefer live recordings of music, or do you have no preference?

Any or all the questions can be skipped as preferred if at least 1 answer is given to questions 1, 2, or 3. Definitions of any of the music attributes (eg, electric and energetic) are provided if necessary and are available on the web-based tool.

The reported preferences are entered into a POMI web-based tool (Figure 2) to generate a personalized music playlist on Spotify, with a tempo restriction of 60-80 bpm as recommended [11]. Music is then played for 20 to 30 minutes via a smart device (iPad, 8th generation).

At all times, patients can control the music (eg, skip a song or stop the music, either briefly or permanently) by accessing the iPad themselves or communicating with the student researcher. Patients unable to self-report are continually monitored by the student researcher while the music is playing so that any nonverbal reaction to the music, indicating such dislike of the music, would lead the student researcher to stop the music immediately.

### Control Intervention

The CTL consists of providing a 20-30–minute period without music either while wearing headphones (Bose, QuietComfort 35) or with the head resting on a music pillow (MusiCure, hospital-grade), which is consistent with the mode of delivery for the POMI. Adult patients admitted to the ICU and able to self-report can choose 1 of the 2 modes of delivery. Patients unable to self-report are given the music pillow.

### Washout Period

To allow for any pain-reducing effect of the POMI to dissipate before the CTL, a washout period of at least 4 hours is scheduled between both intervention periods, based on previous data on the duration of the analgesic effect of music on pain [32].

### Video Recordings

Video will be recorded for the duration of the intervention period and at each pain assessment time point. These video recordings will be used to have an independent member of the research team evaluate: (1) the Critical-Care Pain Observation Tool (CPOT) scores for each patient participant (to ensure blinding of the research team member interrater to sequence allocation) and (2) the intervention fidelity.

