#### Feasibility of Intervention

The items for the assessment of intervention feasibility include (1) time spent (in minutes) creating the individualized playlist; (2) the presence or absence of any issue with headphone or pillow use; (3) the presence or absence of any issue with music delivery; (4) the presence or absence of skipping one or more songs from the generated playlist; (5) the presence or absence of any environmental noise (eg, alarms and voices) during intervention delivery; (6) the presence or absence of any POMI interruptions; (7) whether the patient participant received the full duration of the POMI; (8) the dose (duration in minutes) of the music delivered; (9) the characteristics of the music delivered (eg, music genres).

Additionally, as part of the feasibility of the intervention, the fidelity of the intervention will be assessed based on specific criteria [39] and will include meeting with participants to discuss music preferences, producing a personalized playlist, and playing music once at least for 20 minutes. Any issues with the delivery of the POMI will also be recorded.

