#### Feasibility and Fidelity of Intervention

Descriptive statistics will be obtained to compute the frequencies for each of the intervention feasibility items. The POMI will be considered a feasible intervention if there are no issues in over 50% of the items for the assessment of the intervention feasibility (as listed above) for at least 80% of the patient participants in each group [48]. Regarding the fidelity of the intervention, descriptive data will be computed on the amount of time spent creating the music playlists (≤10 minutes), delivery of the overall POMI (use of headphones or pillow), as well as the amount of time the music will be listened to (once, for at least 20 minutes). The percentage of items completed on the fidelity checklist will also be computed in order to ensure that at least 80% of the intervention fidelity items will be delivered as planned, yet to allow for a certain amount of flexibility, if needed [48,49].

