### Ethics Approval

Ethics approval was submitted in July 2021 and approved in December 2021 (Project #2022-3005). Participation in this research project is voluntary and ongoing for all participants. Participants are free to refuse to participate and may withdraw from this research study at any time, without having to give a reason, and without any consequence to them now or in the future. The participant’s decision not to participate in the study, or to withdraw from it, will have no impact on the quality of care and services to which they are otherwise entitled. Participants are free to refuse to answer any question and remain in the study. Participants are free to refuse to be video recorded.

For a patient who is unable to consent to participate in the study, a family member representative will provide the written consent on behalf of the patient. From this time and until the patient participant is discharged from the ICU, the student researcher will follow up on the ICU adult patients who were unable to consent to determine if they regain the ability to consent for themselves. In the case where a patient participant who was previously unable to consent regains the ability to consent at any time, before or after the intervention, the student researcher will present the research project and the information and consent form to allow the ICU adult patient to make an informed decision regarding their participation in the study.

The data collected from a participant as part of this study, excluding the video recordings, could be used for future research projects related to this study only with the participant’s explicit permission. The results of the research study, excluding video recordings, may be presented at conferences, published in specialized journals or be the subject of scientific discussions, or be used for teaching purposes. No identifying information will be published in any way.

At any time, participants have the right to consult their study file in order to verify the information gathered and to have it corrected if necessary. All study data will be stored safely for 10 years, after which time they will be permanently destroyed by being either shredded or permanently deleted from the server.

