## Discussion

### Methodological Strengths

One strength of this study is the evaluation of the intervention acceptability from multiple sources: ICU patients, families, and nursing staff. This will allow us to gain access to the different perspectives of the various stakeholders and acquire a more comprehensive understanding of the overall acceptability of the intervention. The crossover design is another strength as it allows each patient participant to be their own control, thus reducing confounding factors that are usually present in between-subject designs [50,51]. Moreover, the crossover design will allow for patient participants able to self-report to share their preference between the POMI and the CTL because they will experience both interventions. Information about participant preference will add rich qualitative data beyond the quantitative comparison of preliminary efficacy [41,51]. The crossover design is relevant to use during procedures that are planned within a short period of time (eg, molar extractions at 2 different times) [50]. In addition to intervention comparisons and patient participant preferences, we will be able to determine the pain and distress differences individually (numerically) and compute the proportion of patient participants for whom the treatment was effective in reducing pain by more than 1 point on a 0-10 NRS, for example [51]. The crossover design will also enable us to describe whether any reduction in pain or distress was qualified as meaningful by the patient participant (for those able to self-report). These data could later contribute to the understanding of the minimally clinically significant difference in procedural pain in the adult ICU population [51]. Knowing that patient participants will receive both interventions as part of the crossover design may allow them to think more objectively about pain levels in each intervention period (thus minimizing the placebo effect) compared to if they participated in a parallel-group trial, in which the patient participants’ hope to receive the intervention may influence their pain rating [50]. Finally, blinding patient participants unable to self-report will reduce the risk of bias based on these participants’ expectations of music efficacy to reduce pain.

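### One rater scores CPOT blind and also rates fidelity from recordings that include the intervention period, so the CPOT blind is not protected as written

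*Protocol article*

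**What the plan says.** The protocol article describes the footage under Video Recordings: "Video will be recorded for the duration of the intervention period and at each pain assessment time point". The same paragraph names its user and purpose: "These video recordings will be used to have an independent member of the research team evaluate" two things, the CPOT scores and, in the same sentence, fidelity. The aim attached to the CPOT task is "to ensure blinding of the research team member interrater to sequence allocation) and (2) the intervention fidelity". The rater is in the singular, and no second rater is mentioned for either task.

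Fidelity is defined elsewhere. Feasibility of Intervention lists "meeting with participants to discuss music preferences, producing a personalized playlist, and playing music once at least for 20 minutes". Feasibility and Fidelity of Intervention adds descriptive data on playlist creation time, delivery by headphones or pillow, and "the amount of time the music will be listened to (once, for at least 20 minutes".

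CPOT is used in all patients, at four time points in each period (Preliminary Efficacy of POMI on Acute Pain). Patients able to self-report also rate pain intensity and distress. Those unable to self-report have CPOT only.

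**The concern.** The sentence that sets out to blind the CPOT rater also gives that rater a task that cannot be done blind. Someone who has watched the intervention footage to confirm that music played for 20 minutes knows which period was POMI. If that person then scores CPOT, or revises earlier scores, expectation can enter the ratings.

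At stake is the one pain outcome for which the article arranges a blinded assessor. Intensity and distress are reported by patients whom the article itself describes as unblinded. The student researcher watches over patients unable to self-report while the music plays, so this bedside observer knows the condition. For the 12 patients unable to self-report, in whom the Introduction says the effect of music on pain is unknown, there is no other pain measure.

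**Working it through.** No arithmetic applies and the plan gives no figure to reproduce. The check sets the relevant statements side by side.

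1. **Who rates.** One independent team member does both tasks (Video Recordings).
2. **What that person has.** Footage of the whole intervention period and of each pain assessment (Video Recordings).
3. **What fidelity requires.** The criteria concern music: preferences discussed, a playlist made, music played once for at least 20 minutes (Feasibility of Intervention; Feasibility and Fidelity of Intervention). They apply to POMI and not to the control period, so rating them identifies the POMI period.
4. **What that reveals.** Sequence 1 is POMI then control, and sequence 2 is the reverse (Design). With two periods and two conditions, knowing the condition of one period fixes the other and hence the sequence. This is the information the rater is meant not to have.
5. **Whether anything separates the tasks.** The article states no second rater, no division of footage between the tasks and no scoring order.
6. **Whether CPOT could still be scored blind.** Yes. The four assessments fall at baseline, directly after the session, during turning and half an hour after turning, all outside the session itself. The control period uses the same headphones or pillow (Control Intervention). Assessment clips viewed alone therefore need not show the condition.

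Steps 1 to 4 show that fidelity rating breaks the blind for any CPOT score given afterwards. Step 5 shows that the article does not prevent that order. Step 6 shows that the order is avoidable.

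How a rater's lean would reach the results depends on its form. Preliminary Efficacy specifies Friedman tests across time points within each group, followed by Wilcoxon signed rank tests. A constant shift at all four time points of a period would leave those rankings unchanged, whereas a lean that differs between baseline and later time points would not. The same section also counts lower scores in the music period than in the control period as support for the intervention, even at P<.10. A constant shift in one period would enter that comparison directly.

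**The case against.** The strongest reply is that the article does not say fidelity is viewed first. It names two kinds of footage, and a sensible team would score the assessment clips before turning to the intervention footage. Scoring order and clip handling are details that a condensed article may leave to the full protocol. This stands to the extent that a reader might infer from the dual assignment that CPOT is in fact unblinded. The document does not support that, because the assessments lie outside the session, the devices are the same and an unstated order could preserve the blind. It does not remove the point, because the article does more than leave out a detail: it pairs the blinding aim with a task that defeats it and says nothing to keep them apart.

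Three further readings are tempting, and the document does not carry them.

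- A reader might infer that the claim "blinding patient participants unable to self-report will reduce the risk of bias" is false, because patients who hear music are not masked and the article foresees that "any nonverbal reaction to the music, indicating such dislike of the music, would lead the student researcher to stop the music immediately". Reacting to music is not the same as knowing the study conditions or expecting pain relief, and that expectation is what the claim concerns. The claim can be doubted but is not refuted. It is also a separate matter from the assessor's blind.
- A reader might count "Participants are free to refuse to be video recorded" as a flaw. It is a participant's right, and no refusal rate is given. It matters only in that such patients will have no video score.
- A reader might want the bias in CPOT points. The article gives no standard deviation for CPOT and no basis for the size of a rater's lean, so any figure would be invented.

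The reply is also right that efficacy is secondary. Preliminary Efficacy says these findings will not decide whether a full trial follows, and acceptability and feasibility do not depend on a blinded CPOT.

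**Conclusion.** The point holds as a weakness in how the blind is protected: the video rater's blinding to sequence is stated as an aim, but the fidelity task given to the same person can undo it. It does not establish that any CPOT score was or will be unblinded.

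The consequence is modest and confined to preliminary efficacy. Within that objective it affects the only pain measure for 12 of the 24 patients and the only one shared by all 24. The conclusion assumes that one person does both tasks, as the singular wording says, and that no unpublished procedure fixes the order. If the full protocol already has CPOT locked first or uses separate raters, a sentence saying so settles the matter.

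**What to change.** Cut the T0–T3 assessment clips from the intervention footage, code them without period or sequence labels, and shuffle them. The team member scores and locks all CPOT ratings from these clips before opening any intervention footage for fidelity. Locking should cover all patients, not one patient at a time. Randomization uses blocks of 4 with two patients per sequence in each stratum, so someone who knows the block structure and the sequences of three patients in a block can deduce the fourth.

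Use this video score as the CPOT in the comparison of POMI with control wherever video exists, since the blind helps only if the blinded score is the one compared. Flag patients without video. The change concerns how recordings are handled, so it can still be applied to any footage not yet rated, although recruitment is well advanced.

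The cost is some hours of clip editing and a fixed scoring order, with no extra staff or patients.
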